## Methods

### Overview

We are conducting a feasibility randomized controlled trial (RCT) to evaluate the use of a custom-developed cognitive training program to improve the cognitive function of children aged between 4 and 6 years who were exposed to alcohol in the prenatal stage compared with a control group.

We hypothesize the following:

Post intervention, the intervention group will score higher on psychometric assessments of EFs than the control group.At baseline, alcohol-exposed children (both intervention and control groups) will score significantly lower on psychometric assessments of EFs compared with nonalcohol-exposed children (normative group).Post intervention, the intervention group will score higher on psychometric assessments of EFs than the control group, but lower than the normative group.Post intervention, the intervention group will show greater improvement on psychometric assessments of EFs than the control and normative groups.Improvement in game performance will be correlated with improvement on psychometric assessments of EFs.Improvement in psychometric assessments of EFs will be positively correlated with total time spent playing the game.

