### Study Procedures

Alcohol-exposed children, as assessed by maternal interviews, will be randomized into an intervention or a control group with 40 participants in each group, using block randomization. The maternal interview will contain questions regarding alcohol use just before and during pregnancy, including the number of standard units of alcohol consumed, with 3 standard units being the threshold for determining alcohol exposure. A group of 40 unexposed children will be randomized in a group to provide normative data using individual randomization. An overview of the study design is shown in Figure 1. As the participants are drawn from a low-SES and resource-poor environment, the performance of the normative group will serve as a more suitable gauge of cognitive development in the participants’ specific contexts. This will enable us to better interpret the results of the neurodevelopmental assessments.

The SPIRIT schematic is shown in Table 1. Baseline assessments examining cognitive function will be conducted with all 3 groups. The intervention group will then play the FARR game twice a week for 6 months (40 play sessions in total). Post intervention, all 3 groups will receive follow-up cognitive assessments. Data gathered by the game will also be collected from the intervention group. All participants will start the intervention at the same level of difficulty. They will be given the opportunity to play the game during hour-long sessions facilitated by community workers. Play will, however, be self-directed; participants will be encouraged to play but will be allowed to stop at any time during a session. As participants log into the devices, they will be able to continue at the difficulty level they had previously reached.

There are 4 different stages in the game of increased complexity. After 10 trials in a stage, a participant automatically moves on to the next for 10 trials. After the fourth stage, participants start at the first stage again. The difficulty of each stage varies independently based on a participant’s performance. Getting 8 or more correct increases difficulty, getting fewer than 4 correct decreases difficulty, and otherwise the difficulty remains the same.

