### Data Analysis

For the primary hypothesis, the postintervention scaled scores of the intervention group will be compared with those of the control group. This will be done using a MANOVA with group membership as the predictor variable and the scaled scores of the 5 NEPSY-II domains (see Table 1) as outcome variables. Discriminant analysis will be done on the outcome of the MANOVA with the domain scores as predictor variables and group membership as outcome variables.

During further analysis, the baseline NEPSY-II scaled scores of the intervention and control groups will be pooled and compared with the scores of the normative group. This will also be done using a MANOVA with group membership as the predictor variable and the scaled scores of the 5 NEPSY-II domains (see Table 1) as outcome variables. Discriminant analysis will again be done on the outcome of the MANOVA with the domain scores as outcome and group membership as predictor variables.

Postintervention NEPSY-II scaled scores (see Table 1) of the intervention, control, and normative groups will be compared using a MANOVA. Group membership will be the predictor variable, and domain scores will be the outcome variables. Discriminant analysis will be conducted with the domain scores as outcome variables and group membership as predictor variables.

Difference scores between baseline and postintervention assessments will be calculated for all participants. These scores will be compared using a MANOVA with group membership as the predictor variable and changes in domain scores (see Table 1) as outcome variables. Discriminant analysis will be done on the results with changes in domain scores as outcome and group membership as predictor variables.

For the secondary hypothesis, the improvement in game performance will be quantified as how many difficulty levels a participant has successfully completed in each of the 3 different stages of the game. This will then be correlated with performance in the NEPSY-II domain scores in a covariance matrix using the Pearson correlation coefficient. A separate analysis will be done including only 6-year-old children using the additional domains tested (see Table 1).

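### The game-performance analysis correlates levels completed with NEPSY-II performance rather than improvement, and counts 3 game stages where the game has 4

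*Protocol article*

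**What the plan says.** The Overview (Methods) of the protocol article states the hypothesis as change against change: "Improvement in game performance will be correlated with improvement on psychometric assessments of EFs".

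The Data Analysis section sets out the matching analysis under what it calls the secondary hypothesis. Game improvement is to be measured as "how many difficulty levels a participant has successfully completed in each of the 3 different stages of the game". The next sentence gives the other side of the correlation: "This will then be correlated with performance in the NEPSY-II domain scores", using Pearson coefficients. It does not say whether baseline or postintervention scores are meant, and it mentions neither a difference score nor an adjustment for baseline.

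The paragraph just before it does define difference scores between the two assessments, for every participant. Their only stated use is a MANOVA comparing groups.

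Study Procedures describes the game differently: "There are 4 different stages in the game of increased complexity". The fourth stage is a regular part of play, since "After the fourth stage, participants start at the first stage again", and each stage has its own difficulty track: "The difficulty of each stage varies independently based on a participant’s performance". On the starting point it says: "All participants will start the intervention at the same level of difficulty". Sessions are self-directed, and a child may stop at any time.

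**The concern.** There are two textual problems.

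- **Wrong NEPSY-II variable.** The hypothesis concerns improvement; the analysis names performance. The same section treats change in scores as a separate quantity one paragraph earlier, so the distinction is the protocol's own.
- **Wrong number of stages.** With 4 stages described and 3 analysed, and no stage named as left out, the game variable cannot be computed unambiguously.

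The first matters more. Difficulty rises when a child answers 8 or more of 10 trials correctly, so an abler child climbs faster from the shared start, and a child who plays longer has more chances to climb. Levels completed is therefore a gain that also carries prior ability and exposure. A NEPSY-II score carries prior ability too. The two can correlate through ability alone, and the result could then be read as evidence that training in the game transferred to executive function.

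**Working it through.** The article gives no sample size, power or expected correlation for this analysis, so there is no stated figure to reproduce.

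**Inputs**
- n = 40: only the intervention group plays (Study Procedures); complete data assumed.
- Alpha = 0.05 (Sample Size); two-sided assumed.
- Correlation of levels with prior ability: not given; assumed 0.3 to 0.7 across the two calculations.
- Baseline-to-follow-up correlation of a NEPSY-II score: not given; assumed 0.6 to 0.8.
- NEPSY-II time point: not given; the postintervention score is assumed.

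**Step 1. Direct calculation, no transfer.** Let a be the correlation of levels with the observed baseline score and r that of baseline with follow-up. If levels relate to follow-up only through baseline, the expected correlation is a × r.
- Central case: 0.5 × 0.7 = 0.35. The critical |r| at n = 40 is 0.312.
- Fisher z: atanh(0.35) = 0.365; 0.365 × √37 = 2.22; 2.22 − 1.96 = 0.26; Φ(0.26) ≈ 0.60. The null hypothesis of no correlation is rejected about 60% of the time.
- Low end: 0.3 × 0.6 = 0.18, rejected 20% of the time.
- High end: 0.6 × 0.8 = 0.48, rejected 89% of the time.

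**Step 2. Simulation, no transfer.** A stable trait drives levels and both NEPSY-II scores; 20,000 runs per cell, n = 40. The levels–trait correlation is with true ability, not the observed score, so the figures exceed those of step 1 at nominally equal inputs.

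| Retest correlation | Levels–trait correlation | Mean r with follow-up | Significant and positive | Mean r with change | Significant with change (two-sided) |
|---|---|---|---|---|---|
| 0.7 | 0.3 | 0.25 | 35% | 0.00 | 4.6% |
| 0.7 | 0.5 | 0.42 | 79% | 0.00 | 5.0% |
| 0.7 | 0.7 | 0.58 | 98% | 0.00 | 5.1% |
| 0.8 | 0.3 | 0.26 | 39% | 0.00 | 5.1% |
| 0.8 | 0.5 | 0.44 | 84% | 0.00 | 4.9% |
| 0.8 | 0.7 | 0.62 | 99% | 0.00 | 5.0% |

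Under this model the change score keeps the nominal error rate.

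**Step 3. Baseline adjustment instead of change.** In the step 2 model with retest 0.7 and levels–trait correlation 0.5, levels correlate 0.5 × √0.7 = 0.418 with each score. The partial correlation given baseline is (0.418 − 0.418 × 0.7) / √[(1 − 0.175)(1 − 0.49)] = 0.125 / 0.649 ≈ 0.19. Simulated, it is significant about 22% of the time (roughly 9% to 48% over the table's range). Baseline is a noisy measure of ability, so adjusting for it leaves residual confounding.

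**Step 4. Limit of the change score.** If levels follow the observed baseline score itself, as in step 1, the partial correlation is zero. The correlation with change is then −a√[(1 − r)/2] = −0.5 × √0.15 ≈ −0.19, through regression to the mean. This bias runs against the hypothesis, so it does not manufacture support for it. It is a reason to report both analyses.

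**The case against.** The strongest reply is that performance is loose wording for change. The hypothesis is about improvement, and the sentence before introduces improvement in the game. The game side is also not mismatched: with a common starting level, levels completed is a gain from a fixed point. The figure 3 may be a slip, so it would go too far to say that a stage is dropped. All of this is fair. It does not settle what will be computed, because the same section uses a different term when it means change, and nothing accounts for the missing stage. The common start does not remove the influence of ability or playing time either.

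The percentages rest on assumed inputs, and the move from 60% to 79% between steps 1 and 2 shows how far they depend on the model. That stands; only the direction is secure.

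A reader might infer further faults that the article does not support:

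- **Screening.** The Discussion suggests that strong correlations could lead to further studies of the game as a screening tool. A screening tool should track existing ability, so a correlation arising from ability does not undermine that idea.
- **Play time.** The hypothesis that "Improvement in psychometric assessments of EFs will be positively correlated with total time spent playing the game" has no analysis in the article, but a condensed article may leave that to the full protocol or analysis plan.
- **Multiplicity.** The same applies to the absence of a multiplicity rule for secondary correlations in a feasibility trial.
- **Children who turn 6 during the study.** Measures provides for testing them on the extra subtests at follow-up. The analysis for 6-year-olds names a correlation and no improvement score on those subtests, so the missing baseline contradicts nothing stated.

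**Conclusion.** The concern holds on two points. The analysis as worded does not match its hypothesis on the NEPSY-II side, and the stage count contradicts the description of the game. Followed literally, it can yield a positive correlation without any training transfer, provided ability influences both measures. With assumed correlations of 0.5 and 0.7 that happens in about 60% of trials of 40 players, and in 20% to 89% over the range in step 1. None of these correlations comes from the article.

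This is a secondary, within-group association. It should be corrected, but it does not touch the randomised comparison of intervention and control. Nor does it show that the hypothesis is untestable: the difference scores needed are already planned.

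**What to change.** In Data Analysis:

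1. Replace performance in the NEPSY-II scores with the baseline-to-postintervention difference scores that the section already calculates, and correlate these with levels completed.
2. Compute levels completed for each of the 4 stages, or name the stage left out and say why. Make this agree with Study Procedures.
3. As a sensitivity analysis, regress the postintervention score on levels completed with the baseline score as covariate. Note that residual confounding remains if baseline is measured with error, and that the change-score correlation may be pulled downward by regression to the mean.
4. Describe either result as an observational association within the intervention group, not as evidence that training caused the improvement.

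The cost is a change of wording. The NEPSY-II is given at both time points and the game logs are already collected, so no new data, visits or participants are needed.

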### Measures

The primary outcome is EF, as measured using the NEPSY-II psychometric assessment score. The secondary outcomes are (1) game performance, as measured in the game log files, (2) reaction time, and (3) increase in the level of difficulty of the task.

Additional demographic data will be gathered during the recruitment process. In addition to alcohol use, data will be gathered on age, gravidity, parity, years of schooling, and household income.

All participants will be evaluated using a selection of subtests of the NEPSY-II that measure executive functioning and working memory. Cognitive function, focusing on EFs, will be measured using the NEPSY-II [36]. The NEPSY-II is a compendium of tests based on the Luria theoretical approach to neurological assessment. It is individually administered and has been shown to be successful in diagnosing a range of childhood disorders. The subtests of this test can also be selected based on the specific domains to be tested [37].

Scores obtained on the subtests of the NEPSY-II are compared with the scores of a normative group based on age. The normative group of the NEPSY-II was selected to closely match the US population between 3 and 16 years of age [38]. This group will differ significantly from the populations of interest in this study; however, the NEPSY-II is relatively insensitive to language and culture differences. Although the results need to be interpreted cautiously, the test remains clinically useful [39]. Insensitivity to language is an important feature as the study sample will be drawn from a predominantly Afrikaans-speaking community, which could affect test performance [40].

In the standardization of the NEPSY-II, subtests showed adequate-to-high internal validity. There was no significant practice effect with re-administration of the test in a short space of time (around 3 weeks), supporting its use for both the pre- and postintervention assessments in this study [41]. Inter-rater agreement was high on both the objectively and more subjectively scored test, and the reliability of subtests remained stable [38]. The inclusion of the third group of children not exposed to alcohol in pregnancy will help guide the interpretation of results.

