#### Game Log Files

Additional data will be obtained from the log files generated by the game. The file will record error rates and response times for all tasks. Each child will be allocated a numbered tablet or a profile on a specific tablet, depending on what proves the most practical, and the log file will then be associated with their study number.

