Additional exploratory analyses will be done comparing the demographic information of the 3 groups. These data will be drawn from the maternal interview. Demographic data on the mothers of the alcohol-exposed children (both intervention and control groups) will be pooled and compared with nonalcohol-exposed children to ascertain if there were significant differences between the 2 groups. This will be done using 2 tailed *t* tests for independent samples. To account for family-wise errors, Bonferroni-adjusted values will also be calculated. The variables to be analyzed are age, gravidity, parity, years of schooling, and income. Tobacco and drug use will also be compared among the alcohol-exposed and nonalcohol-exposed groups using a chi-square test.

Further exploratory analysis will be done on the game logs. Reaction time in the various stages of the game will be used to conduct an exploratory factor analysis. Looking for common variations among the various game metrics may unearth underlying variables that better explain which EFs are associated with which game tasks. For each participant, their reaction times for the highest level they successfully complete will be used. Using regularized exploratory factor analysis owing to the small sample size, we can examine whether the conceptually different tasks do in fact target different EFs.

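### A factor analysis of game reaction times alone can describe shared and distinct response-time variance across stages, but cannot show which executive function a factor represents

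*Protocol article*

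**What the plan says.** The Data Analysis section introduces this step with "Further exploratory analysis will be done on the game logs" and names the input: "Reaction time in the various stages of the game will be used to conduct an exploratory factor analysis". The value taken per child is also fixed: "For each participant, their reaction times for the highest level they successfully complete will be used".

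Two aims are given. The first is hedged: common variation among the game metrics "may unearth underlying variables that better explain which EFs are associated with which game tasks". The second is firmer: with a regularized factor analysis, "we can examine whether the conceptually different tasks do in fact target different EFs".

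On the data available, the Game Log Files section says: "The file will record error rates and response times for all tasks". The trial's measure of EF is a different instrument: "The primary outcome is EF, as measured using the NEPSY-II psychometric assessment score" (Measures). Only the intervention group, planned at 40 children, has game data.

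A separate analysis in the same section correlates the number of difficulty levels completed in each stage with NEPSY-II scores, and repeats this in the 6-year-olds with their additional subtests.

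**The concern.** The stated input and the stated aims do not match. A factor analysis works on the correlations among the variables entered. If these are all reaction times, a factor says which times vary together. It does not say why, and nothing in the input distinguishes an executive function from general processing or motor speed, or from a demand peculiar to one task.

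The risk lies in interpretation. One dominant factor could be reported as all tasks drawing on one EF, and several factors as tasks drawing on different EFs, although neither conclusion follows from reaction times alone. A larger sample, regularization or more reaction times per stage would not supply the missing reference measure.

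**Working it through.** The article gives no figure for this analysis, so there is none to reproduce. The check sets input against aim and adds three short calculations.

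**1. Does the input carry information on EF?** Assume each of four stage reaction times loads 0.7 on one common factor (the loading is an assumption). The correlation between any two times is 0.7 × 0.7 = 0.49. Let that factor correlate ρ with an external EF score, so that each time correlates 0.7ρ with the score.

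| ρ (assumed) | Correlation among reaction times | Reaction time with EF score |
|---|---|---|
| 0 | 0.49 | 0.00 |
| 0.3 | 0.49 | 0.21 |
| 0.7 | 0.49 | 0.49 |

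A simulation gave the same values. The planned analysis sees only the middle column, which does not change. The information needed to name the factor is in the last column, which is not part of the analysis.

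**2. Can it at least show that tasks differ?** This depends on how many reaction times per stage are entered. Let a shared component account for a share s of variance and a stage-specific component for a share f.

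- *One time per stage.* Four independent functions plus shared speed give a between-stage correlation of s. One shared function with the same loading and no speed component also gives s. With s assumed at 0.3 to 0.5, both structures give correlations of 0.3 to 0.5 and the same factor solution.
- *Several times per stage.* The first structure gives s + f within a stage and s between stages; the second gives s for both. These can be told apart. The stage-specific part f is still unnamed: it may be an EF or some other feature of that task.

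One time per stage is an assumption. The Intervention section says response time is logged per item, and the Data Analysis section does not say how the times are summarised.

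Under that same assumption, the factor-model degrees of freedom are [(p − m)² − (p + m)]/2 for p times and m factors. Study Procedures states "There are 4 different stages in the game of increased complexity", whereas Data Analysis counts three.

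| p | m = 1 | m = 2 |
|---|---|---|
| 4 | (9 − 5)/2 = 2 | (4 − 6)/2 = −1 |
| 3 | (4 − 4)/2 = 0 | (1 − 5)/2 = −2 |

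Without a penalty, no more than one factor is identified. With regularization, a second factor would depend on the penalty.

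**3. What would a link to NEPSY-II achieve?** By Fisher's z with n = 40, the 95% interval is tanh(atanh r ± 1.96/√37). For r = 0.5 this is tanh(0.549 ± 0.322), or 0.22 to 0.70. For r = 0.3 it is −0.01 to 0.56. Power at two-sided 0.05 is about 0.47 for r = 0.3 and 0.92 for r = 0.5 (assumed values of r). The link becomes estimable, but imprecisely.

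**4. Which NEPSY-II scores could serve?** Table 2 lists five subtests for all ages. Only Statue falls under attention and executive function; one is under language and three under memory and learning. The four additional attention and executive subtests are for 6-year-olds only, a subset of the 40 whose size is not given. The Intervention section names four target functions: inhibitory control, cognitive planning, set shifting and working memory. The subtests available to every child cannot be assumed to mark each of them.

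**The case against.** The strongest defence is that this is a hedged, exploratory look that touches no stated hypothesis, and that an article need not spell out how factors will be interpreted. The exploratory label stands and keeps the weight low. But the article itself fixes both the input and the claim drawn from it, so the mismatch is in the text and is not a detail left to a fuller document.

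Factors could be labelled from what each task was designed to train. That would assume what the analysis is meant to examine.

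The mention of various game metrics might bring in error rates. These are not an independent EF measure either. They may also vary little at a level the child has passed, since 8 or more correct out of 10 raises difficulty, although successful completion is not defined.

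Three stronger readings are tempting, and the document does not support them:

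- *The trial has no link between game and EF.* It has one: levels completed are correlated with NEPSY-II scores by stage. That analysis uses neither reaction times nor factors, so it cannot name the factors.
- *The factor analysis can say nothing about whether tasks differ.* This goes too far. With several times per stage it can explore whether stages have distinct variance, which is part of the second aim.
- *The decision to redesign the game rests on this analysis.* The Discussion speaks of the study's data in general and does not mention the factor analysis.

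**Conclusion.** The point holds in limited form. As described, the factor analysis can show whether stages share reaction-time variance or have their own, but not which EF, if any, a factor represents. That conclusion follows from the choice of input and does not depend on sample size or on the number of times per stage. The further limit, that distinct functions plus shared speed cannot be told from one shared function, holds only if a single reaction time per stage is entered. The numerical illustrations rest on assumed loadings and variance shares. The consequence is confined to how one exploratory result is worded and read; the primary outcome is unaffected.

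**What to change.** Correlate the reaction-time factor scores or stage scores, and the logged error rates where they vary, with the NEPSY-II subtests already collected, and report each correlation with its interval. State that Statue is the only all-ages subtest listed under attention and executive function, and that results for the four additional subtests rest on the 6-year-olds alone, so their intervals will be wider than those for 40 children. Name a factor as an EF only where such a relation is seen. Otherwise restate the aim as describing shared and distinct reaction-time variance across stages. It would also help to say how many reaction times per stage enter and to reconcile the stage count.

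The cost is a little extra exploratory analysis on existing data, or a change of wording. The price of the first option is wide intervals, so any naming of factors would remain tentative.
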